## Intervention

The intervention takes place over a 12-week period followed by a 12-week follow-up. Each intervention consists of five individual appointments (week 1, 3, 5, 7, 10; duration: first appointment 60 min, following 45 min). The study timeline is presented in Fig. 2.

**Fig. 2. f2:**

Study timeline.

### Group 1: Mediterranean diet

Participants in this group are asked to change their food intake towards the Mediterranean diet. The Mediterranean diet is composed of at least two portions of vegetables and fruit, (whole-grain) cereal products and olive oil as the main source of fat in every meal. Two portions of dairy products and olives, nuts or seeds are consumed daily and at least two portions of legumes and fish, two to four eggs and two portions of white meat each week. The intake of sweets and red and processed meat is limited to twice and once a week, respectively^(34)^. Aspects such as sociability, seasonality and physical activity, which are part of some definitions of the Mediterranean diet^(35)^, are not addressed. The intervention is based on a food diary, which the participant will be filling out for 3 days in advance. Like this, personnel dietary preferences and habits (i.e. vegetarian diet, aversion to certain foods) can be considered throughout the intervention to increase practicability and long-term adherence. Personal goal setting and individual obstacles are addressed. Participants also receive information material, tips for grocery shopping and goal setting, as well as recipes and a checklist. Typical foods of the Mediterranean diet (e.g. olive oil, nuts, legumes, whole-grain pasta) are handed out at the end of each appointment.

### Group 2: mindful eating

The training for mindful eating does not address changing food choices but rather focuses on eating behaviour in terms of the way the food is eaten. It addresses eating behaviour in relation to mindfulness, appreciation, enjoyment and values. Each of the appointments provides instructions for practical implementation in everyday life. The food diary completed for 3 days in advance of the first appointment is discussed with regard to eating behaviour in order to identify individual approaches to establish mindful eating. Participants receive information material and tips for goal setting, as well as instructions and materials for practical exercises. Either materials for completing the tasks (e.g. growing sprouts at home) or a voucher of the same value as the food in groups 1 and 3 are handed out. The intervention is based on the programmes ‘Michael Pollan Teaches Intentional Eating’^(36)^
, ‘MB-EAT’ (Kristeller *et al.*, 2011^(37)^) and ‘Jon Kabat-Zinn Teaches Mindfulness and Meditation’^(38)^.

### Group 3: combination of Mediterranean diet and mindful eating

The third intervention group combines the interventions of groups 1 and 2 by providing nutritional intervention regarding the Mediterranean diet as in group 1 and addressing the same content on mindful eating as in group 2. The content and practical exercises refer to Mediterranean food. The food diary is discussed with regard to food choices, as well as the eating environment and behaviour. Participants receive the same information materials as groups 1 and 2 and the same tools for home practice as in group 2 and Mediterranean foods as in group 1 in the other sessions.

### Group 4: befriending

The control group consists of a befriending intervention, which represents a standard form of control group developed for psychological trials^(39)^, which has prior been successfully used as an active control in nutritional interventions investigating psychological outcomes^(17,19)^. Following the same scheme, it provides the same time and attention as the other intervention groups (i.e. five individual appointments), allowing for control of unspecific effects of the intervention. Positively perceived topics of everyday life and personal interests are discussed (e.g. hobbies, vacations, sports). In addition, activities such as board games and walks can be undertaken. Usage of these activities will be recorded. Like group 2, the participants also receive a voucher card with the same value as the food handed out in groups 1 and 3.

On request, all participants receive the documents of the other intervention groups after follow-up completion. No further post-trial care is foreseen. In case of reporting of adverse events, intervention will be adjusted to meet the personal needs of participants. The participants’ health has the highest priority during the whole study. In case of any serious health risks, participants may withdraw and be referred to further care.

## Outcome measures

Outcomes will be measured at baseline (T0), post-intervention (T1, 12 weeks) and after the follow-up period (T2, 24 weeks) (see Fig. 1). Outcome measurement will be conducted by blinded study personnel.

### Primary outcome

As a primary outcome, depression severity is assessed using the BDI-II. This self-report questionnaire records the occurrence of various depressive symptoms in twenty-one questions on a 4-point scale. The BDI-II score ranges from 0 to 63, with higher scores indicating higher depression severity^(40)^.

### Secondary outcomes

#### Remission

Remission rates will be assessed as the number of patients who no longer show depressive symptoms, defined as BDI-II < 9.

#### Depression severity, rater-assessed

In addition to self-rating, the severity of depression is also measured by blinded outcome assessors. Therefore, the Montgomery Asberg Depression Rating Scale (MADRS) is conducted at T0 and T1. Assessment is done following the questionnaire guidelines in a face-to-face setting or via telephone by a psychologist. It consists of ten questions that are answered on a scale from 0 to 6, resulting in a total score of 0–60, with higher scores representing higher depression severity^(41,42)^.

#### Quality of life

Health-related quality of life is measured using the Short Form-36 Health Survey. It consists of thirty-six items, resulting in a mental and physical sum score, which can be further divided into the subscales vitality, physical functioning, physical pain, general health perception, physical role function, emotional role function, social role function and psychological well-being. Higher scores indicate a higher quality of life^(43)^.

#### Self-efficacy

Self-efficacy is measured using the general self-efficacy expectation scale. It measures the optimistic belief in competence in ten items and results in a total value between 10 and 40, with a higher value indicating a greater expectation of self-efficacy^(44)^.

#### BMI

Body weight is measured using the OMRON BF511 scale. Height is measured in the horizontal plane using a portable stadiometer. All measurements are conducted without shoes and in light clothing. The BMI is calculated using the formula BMI = body weight [kg]/(height [m])^2^.

#### Waist:hip ratio

The waist circumference is measured in the horizontal plane in the middle between the costal arch and the upper edge of the iliac crest, and the hip circumference is measured at the point of the largest circumference of the hip or buttock region. Both measurements are taken twice, and their mean value is calculated. If the measurements differ by more than 1 cm, they are repeated. The waist:hip ratio is calculated from the mean values.

#### Body composition

Participants’ body composition is determined using an OMRON BF511 bioelectrical impedance analysis scale. It gives information on body fat and muscle as a percentage of body weight.

### Adherence

#### Adherence to Mediterranean diet

Adherence to the Mediterranean diet is measured using the Mediterranean Diet Adherence Score (MEDAS). It consists of fourteen questions regarding the eating habits of various foods of the Mediterranean diet. The score ranges from 0 to 14, with higher values indicating higher adherence to the Mediterranean diet^(45)^.

#### Adherence to mindful eating

Mindful eating is measured using the Mindfulness Eating Inventory (MEI). The questionnaire comprises the subscales awareness of sensory experience during eating, eating in relation to awareness of stomach fullness, awareness of eating motives and triggers, connectedness, non-reactive attitude and attention focused on eating. The thirty items are evaluated on a 6-point Likert scale. The sum score is divided by the number of items, resulting in a score from 1 to 6, with higher scores indicating higher adherence to mindfulness eating^(27)^.

### Safety

To analyse the safety of the interventions, adverse events will be assessed in structured questionnaires at T1 and T2. Time point, duration (in hours or days) and strength (on a scale from 1 to 10) are recorded. In addition, participants are asked whether they see a connection between the occurrence of the adverse event and the intervention. Occurrence of serious adverse events is reported to the responsible centre for clinical studies within 24 h.

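### Non-serious adverse events are asked about on schedule only at weeks 12 and 24, after the last appointment, so capture during the intervention rests on long recall, unsolicited reports and return for T1

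*Protocol article*

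**What the plan says.** All references are to the protocol article.

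- **Safety**: for the safety analysis, "adverse events will be assessed in structured questionnaires at T1 and T2". For each event, "Time point, duration (in hours or days) and strength (on a scale from 1 to 10) are recorded", and participants are asked whether they see a link to the intervention. Serious events follow a separate route: "Occurrence of serious adverse events is reported to the responsible centre for clinical studies within 24 h".
- **Outcome measures**: T1 is at 12 weeks and T2 at 24 weeks.
- **Intervention**: "Each intervention consists of five individual appointments", held in weeks 1, 3, 5, 7 and 10.
- **Group 4: befriending** (closing paragraph, which addresses participants of all arms): "In case of reporting of adverse events, intervention will be adjusted to meet the personal needs of participants". It adds: "In case of any serious health risks, participants may withdraw and be referred to further care".
- **Sample size calculation**: 64 participants, sixteen per arm, with an allowance of 20 % for dropout.
- **Data management**: there is no data monitoring committee.
- **Discussion**: dropouts and adverse events are to be analysed systematically.

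No section describes asking about adverse events at the appointments or when a participant withdraws.

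**The concern.** The article names the time points for adverse-event assessment, so this is a stated schedule and not simply detail left out of a short text. Both time points come after the last session.

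This matters for three reasons. First, the form asks for timing, for duration down to hours and for a strength rating, and at T1 all of that must be recalled over the whole intervention. Second, an event that first comes to light on the T1 form comes too late to change any of the five sessions, so the commitment to adjust the intervention works only for events that participants raise on their own. Third, the form reaches only people who return for T1 or T2. If stopping is related to an event, or if loss differs between arms, the comparison of event frequencies across the four groups is biased. Without a monitoring committee, these questionnaires are the only systematic safety source the article describes.

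**Working it through.** The article gives no numerical safety figure to reproduce. The check is of the timeline and of the number of participants at risk of having no data.

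**1. Timeline.** Inputs: appointments in weeks 1, 3, 5, 7 and 10 (Intervention); questionnaires in weeks 12 and 24 (Outcome measures, Safety).

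- Scheduled adverse-event questions from week 1 to week 10: 0.
- Gap from last appointment to first question: 12 − 10 = 2 weeks.
- Gap from first appointment to first question: 12 − 1 = 11 weeks, or about 12 if counted from baseline.
- Look-back at T2: 24 − 12 = 12 weeks.

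**2. Recall if the form is also used at the appointments.** The intervals between successive forms would be 3 − 1 = 2, 5 − 3 = 2, 7 − 5 = 2, 10 − 7 = 3 and 12 − 10 = 2 weeks. The longest recall during the intervention falls from about 12 weeks to 3.

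**3. Participants possibly without any adverse-event data.** Inputs: N = 64, sixteen per arm, 20 % dropout (Sample size calculation).

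- Overall: 64 × 0.20 = 12.8, about 13.
- Per arm: 16 × 0.20 = 3.2, about 3.

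This is an upper bound under the planned dropout. It is reached only if every dropout occurs before T1 and none of these participants answers a later questionnaire. It would be zero if all who stop the sessions still complete T1.

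**4. Participants with an event among those lost.** The article gives no event rate. As an assumption, take 5 % to 30 % of participants with an event and the same risk in dropouts as in others:

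- 12.8 × 0.05 = 0.64
- 12.8 × 0.30 = 3.84

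At the upper bound in step 3, about 0.6 to 3.8 participants with an event would go unrecorded. The number would be higher if events are a reason for leaving, and lower if some dropouts still return the form.

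**5. Safety against the adjustment commitment.** The adjustment is triggered by a report from any source. The only scheduled source falls in weeks 12 and 24, after the sessions have ended. Spontaneous reports at the sessions are therefore the only route by which a non-serious event can lead to a changed session, and the article describes neither a prompt nor a record for them.

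**The case against.** A reader might infer more than the article supports, and the other side is right on several counts.

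- *That early events are missed.* The T1 form records when each event occurred and how long it lasted, so it looks back over the intervention and can pick up early events. What remains is recall error and possible under-reporting. The article gives no figure for the size of that error, nor for its direction where strength is concerned.
- *That events cannot trigger the adjustment.* The commitment is tied to reporting, not to the questionnaire, and participants have five one-to-one sessions in which to report. The two sections do not contradict each other. What is absent is scheduled elicitation.
- *That serious events also wait until week 12.* They have their own 24-hour rule, and withdrawal with referral is provided for.
- *That 13 participants will have no data.* The 20 % is a sample-size allowance. The article does not say that it means loss before T1, and no section links dropout to adverse events.

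It can also be said that counselling, mindfulness training and befriending are low-risk, that the article gives reasons for having no monitoring committee, and that an article may leave the logging of spontaneous reports to the full protocol. The low risk lowers the urgency. The last argument carries less weight here because the article itself fixes the time points. If collection at visits exists, one added sentence in Safety would settle the matter.

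**Conclusion.** The point holds in a limited form. Scheduled elicitation of non-serious adverse events is confined to weeks 12 and 24, after the last appointment in week 10. Systematic capture during the intervention therefore relies on recall of up to about 12 weeks, adjustment of the intervention relies on unsolicited reports, and participants lost before T1 have no described capture.

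The last group numbers between 0 and about 13 of 64, assuming dropout at the planned 20 %. Bias in the between-arm safety comparison is possible but not shown: it requires loss that is related to events or that differs by arm, and the article gives no data on either. The primary efficacy analysis is not affected. This is a worthwhile, inexpensive improvement to the stated safety analysis, not a fault that undermines the trial.

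**What to change.** Have participants complete the same structured adverse-event form at each of the five existing appointments in all four arms, and once at withdrawal (by phone or digitally if need be). Keep T1 and T2, and use all of these data in the safety analysis. The form should be self-completed, to limit the influence of providers who know the allocation. If collection at visits is already in place, state it in Safety so that this section and the commitment to adjust the intervention fit together.

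The cost is a few minutes per visit and one REDCap form. The drawback is collection in an unblinded setting, equal across arms. How care responds to a reported event stays with the investigators.

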### Further data collection

Further data collected contains demographics (T0), a 3-day food diary (T0, T1) and attendance to intervention. Also, information about the usage of co-interventions and the need for psychotherapy is collected at every time point (T0, T1, T2).

### Secondary analyses

#### Mediator and moderator analysis

Weight reduction, quality of life and self-efficacy were identified as potential mediators^(24,46–48)^. Treatment adherence, assessed as the number of intervention appointments attended, is examined as a potential moderator. Additionally, exploratory analyses of mediators and moderators with group allocation as the independent variable will be conducted.

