## Randomisation

After inclusion, participants are randomised to one of the four intervention groups. Randomisation is performed using a randomisation list with varying block lengths (4, 8, 12) created by the programme R. Group allocation is carried out by members of the research staff via RedCap. Therefore, allocation concealment is given. Severity of obesity (obesity grade 1: BMI 30–35 kg/m^2^; obesity grade 2–4: BMI ≥ 35 kg/m^2^) and severity of depression (moderate depression: BDI-II 20–28; severe depression: BDI-II ≥ 29) are defined as strata. Participants are assigned to one of the four intervention groups in a 1:1:1:1 ratio. Participants will be informed about the group assignment at their first intervention appointment.

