## Statistical analysis

The statistical analysis will be carried out using the programme R version 4.4.0. As a significance level, p ≤ 0·05 is defined. Data will be analysed as an intention-to-treat analysis. To handle missing data, the ‘missForest’ package in R will be used. This package implements a non-parametric imputation method based on random forests. This approach iteratively imputes missing values using a predictive model that leverages relationships among observed data while accounting for both continuous and categorical variables. Default settings for the algorithm will be used, which automatically selects the optimal number of trees and variables per split to maximise imputation accuracy. The primary outcome parameter is analysed confirmatory using a two-factorial ANCOVA, in which the main outcome parameter is modelled as a function of the two factors – mindful eating (yes/no) and Mediterranean diet (yes/no) – and the respective baseline values (linear covariates). Both main effects of the interventions and interactions are considered. Secondary outcomes will be exploratory (without correction for multiple testing) and analysed using the same models as the primary outcome. To estimate the clinical significance of the results, change scores and effect sizes (Hedges’ g) are calculated for between-group comparisons. The clinical relevance of the results is examined by comparing the number of participants who achieve a clinically relevant improvement of at least 5 points^(51)^ on the BDI-II between the groups at week 12 and week 24 using a logistic regression adjusted for the BDI-II baseline value (random effect). The same model is used to compare the number of patients between the groups who reach remission of depression at week 12 and week 24 (BDI-II < 9).

Mediator and moderator analyses are conducted with the PROCESS Package^(52)^. For the mediator analysis, the indirect effect of an independent variable on a dependent variable via a mediator and its significance are tested using the bootstrap method. Mediation paths can be identified and quantified with consideration of control variables. Concerning moderator analysis, the relationship between the moderator and the independent variable is analysed using product terms in the regression model. Strength and direction are determined using coefficients and statistical significance using the bootstrap method.

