## Data management

Due to the nature of nutritional intervention, participants and providers cannot be blinded. Participants will learn about their group allocation at their first intervention appointment. Outcome measurements and data analysis will be conducted blinded. Questionnaires will be filled out digitally or on paper.

Study data are collected and managed using REDCap (Research Electronic Data Capture) electronic data capture tools hosted at meDIC/University Hospital Tuebingen^(53,54)^. REDCap is a secure, web-based software platform designed to support data capture for research studies. Data management will be in accordance with data safety guidelines, and data collection and storage will be performed in accordance with Good Clinical Practice Guidelines. There will be no data monitoring committee for the study because of the unblinded and monocentric design and because interventions are delivered only in the short term, and no harm is suspected.

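### Session attendance is tested as a moderator although it arises after randomisation, so its product term can show moderation where none exists

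*Protocol article*

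**What the plan says.** The section Mediator and moderator analysis fixes the variable: "Treatment adherence, assessed as the number of intervention appointments attended, is examined as a potential moderator". The section Statistical analysis fixes the method: "the relationship between the moderator and the independent variable is analysed using product terms in the regression model". Neither section describes any handling of the fact that this variable is observed only after allocation.

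Three other places bear on how attendance comes about:

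- Intervention: "Each intervention consists of five individual appointments", held in weeks 1, 3, 5, 7 and 10. This applies in all four groups, including befriending.
- Randomisation: "Participants will be informed about the group assignment at their first intervention appointment".
- Data management: "participants and providers cannot be blinded".

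On mediators, the article says: "Weight reduction, quality of life and self-efficacy were identified as potential mediators". It then adds that "exploratory analyses of mediators and moderators with group allocation as the independent variable will be conducted", without listing the variables.

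**The concern.** An effect-moderator analysis keeps the protection of randomisation when the moderator is fixed before allocation. Within each level of a baseline variable the arms are still comparable. Attendance does not have this property. The sessions come after randomisation, and from the second one on the participant knows the arm. Content differs between diet counselling, mindful-eating exercises, their combination and befriending. Participants who attend all five sessions of one programme may therefore be a different kind of patient from those who attend all five of another.

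At stake is a sentence in the results paper saying that an intervention works better in people who attend more. Such a sentence could come from selection alone, and readers would probably take it as evidence on dose.

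**Working it through.** The plan gives no figure for this analysis, so there is nothing to reproduce. The check asks when the product term goes wrong and by how much.

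**Algebra.** Let Y be the BDI-II outcome, A the randomised factor, M the number of sessions attended and U an unmeasured prognostic course with coefficient b on Y. Let the treatment effect be a constant t for everyone, so that there is no moderation. Then

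E[Y | A=1, M=m] − E[Y | A=0, M=m] = t + b × (E[U | A=1, M=m] − E[U | A=0, M=m]).

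The product term estimates how this difference changes with m. It is zero if the slope of U on M is the same in both arms, and otherwise it is b × (slope in arm 1 − slope in arm 0). Post-randomisation status alone does not create the bias. The relation of attendance to prognosis has to differ by arm.

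**Inputs.** From the document: N = 64 (Sample size calculation), five sessions (Intervention), significance level 0.05 (Statistical analysis; two-sided assumed). Assumed, because the document gives nothing: U correlates 0.5 with outcome (b = −0.5), and attendance = round(4.2 + a × U + 0.8 × e), cut to 0–5, with e standard normal. Mean attendance is then about 4.1 of 5. The strength a is a1 in the diet arms and a0 in the no-diet arms. The treatment effect is zero and there is no moderation.

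**Expected size.** Ignoring rounding and cutting, the slope of U on M in an arm is a/(a² + 0.8²). For a = 0.8 it is 0.8/1.28 = 0.625; for a = 0.4 it is 0.4/0.80 = 0.50; for a = 0 it is 0. The spurious product term, in outcome SD per session, is then:

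- equal strength (0.8, 0.8): −0.5 × (0.625 − 0.625) = 0
- half strength in controls (0.8, 0.4): −0.5 × (0.625 − 0.50) = −0.06
- diet arms only, weaker (0.4, 0): −0.5 × 0.50 = −0.25
- diet arms only, stronger (0.8, 0): −0.5 × 0.625 = −0.31

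**Simulated rejection rate of the product term** (nominal 5%, 4000 trials per setting):

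| Relation of attendance to course (a1, a0) | Rejected |
|---|---|
| None (0, 0) | 5.1% |
| Equal in all arms (0.8, 0.8) | 5.3% |
| Half as strong in no-diet arms (0.8, 0.4) | 6.0% |
| Diet arms only, weaker (0.4, 0) | 11.6% |
| Diet arms only, stronger (0.8, 0) | 19.6% |
| Reversed in no-diet arms (0.8, −0.4) | 52.9% |

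**Second attendance model.** Here attendance is binomial (5 sessions, probability around 0.8), the effect is constant at 0.86 SD, and the regression also contains the second factor, the factorial interaction and the baseline score. At N = 64 the rates were 4.7% (no relation), 5.0% (equal relation) and 23.7% (active arms only). The active-arms-only rate was 18.4% at N = 52, roughly the size after 20% dropout, and 90.3% at N = 400. Because the error grows with sample size, it is bias and not small-sample noise.

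**The case against.** The strongest reply is that the artefact needs attendance to be selected differently by arm, and nothing in the document shows that it will be. All groups have five appointments. Befriending follows the same scheme with equal time and attention and a voucher of matching value. The no-diet level of the factor also contains the mindful-eating group, which has structured sessions and home exercises, so the factorial contrast is not counselling against board games. If patients who do well or badly attend differently to a similar degree everywhere, the test stays at 5 to 6%. This stands, and it limits the size of the point. It does not make the product term a randomised comparison, and in an unblinded trial with different session content equal selection cannot be taken for granted.

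A second reply is that this is a secondary analysis. That stands too.

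A third is that the word introducing the further exploratory analyses suggests the main moderator analysis may use an independent variable other than allocation, which the article does not name. The simulations above take the arm as that variable. If it were a post-baseline adherence score, both parts of the product would be post-randomisation, so this reply does not remove the problem.

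A reader might infer three stronger points that the document does not support:

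- That the question of what is eaten versus how it is eaten would go unanswered. The randomised main effects in the primary factorial ANCOVA address it.
- That a false-positive rate near 53% is typical. It needs reversed selection in the control arms, for which the document gives no reason.
- That leaving the diet and mindful-eating adherence scores (MEDAS, MEI) out of the named mediators is an error. The open exploratory sentence may cover them, and a full list is commonly left to the full plan.

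**Conclusion.** The point holds in a conditional form. The article commits to testing a post-randomisation variable as a moderator by a product term, and that test does not have the protection of randomisation. Its false-positive rate stays near nominal (about 5 to 6%) if attendance relates to prognosis equally or similarly across arms. It rises to about 12 to 20% if the relation exists in the diet arms only, and the second attendance model puts that case slightly higher, at 24%. All these rates rest on assumed strengths of association and assumed attendance models. The confirmatory intention-to-treat ANCOVA is untouched. The harm is confined to a secondary claim about who benefits.

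**What to change.** Remove attendance as a moderator and report it descriptively by arm. If an estimate of effect among attenders is wanted, use a complier-average analysis with the randomised arm as instrument. It should name the number of sessions that counts as compliance, state its assumptions (including that assignment has no effect below that number) and acknowledge that the estimate will be imprecise with sixteen participants per group.

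Restrict moderators to baseline variables already collected, for example BDI-II, BMI, MEDAS and MEI. State which independent variable the main mediator and moderator analyses use.

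Optionally, name change in MEDAS and MEI as mediators, since these scores measure what the interventions set out to change. An analysis of the week-24 BDI-II adjusted for the week-12 BDI-II should not be used for this, because it removes any mediated benefit already present at week 12.

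The cost is wording in the analysis plan. No new data are needed.
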